### 2.2. Patients

All patients referred to the Department of Respiratory and Sleep Medicine at Hedi Chaker University Hospital of Sfax-Tunisia, for suspected OSAHS will be screened for eligibility between January 2025 and July 2025. Sixty patients will be included. The study will be terminated by December 31^st^, 2025.

Patients will be determined eligible if they are aged 18 years old and above and newly diagnosed with severe OSAS (obstructive apnea-hypopnea index **(OAHI)** ≥ 30 events/ h) as revealed by an overnight type III polysomnography **(PSG)**.

Patients who have previously received CPAP therapy will not be included in the study. Additional exclusion criteria are refusal to participate, illiteracy, pregnancy, major mental disorders, severe heart failure with systolic fraction ejection **(SEF)** < 45%, severe neuromuscular diseases and oxygen supplementation.

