#### 2.3.4. Outcome measures.

Our prespecified primary outcome is CPAP adherence measured in h/night at 1, 3, and 6 months after starting CPAP therapy. Our secondary outcome is functional status at the 6-month follow-up, which includes snoring, nasal obstruction symptoms, subjective quality of life, fatigue, emotional status, cognitive function, insomnia and EDS.

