### 2.6. Protocol study

After a nocturnal polygraph recording showed severe OSAHS, the patient will be seen by a sleep doctor the following day. The doctor will explain the diagnosis and the need for CPAP therapy. The patient will then complete an informed consent form to participate in the study and be randomly assigned to either the usual care (n = 30) or the TPE group (n = 30). Additionally, the patient will fill out a questionnaire covering sociodemographic data, health status, NOSE questionnaire, WHO-5 questionnaire, HAD questionnaire, FSS questionnaire, MoCA questionnaire, ESS questionnaire and ISI questionnaire. Following this, the patient will be scheduled to start CPAP therapy within 1–2 weeks after the nocturnal polygraph recording.

Following the TPE session, patients in the TPE group will be provided with CPAP devices to take home. They will be advised to call the sleep nurses if they experience any side effects. The phone line will be available on weekdays from 9:00 am to 4:00 pm, and patients can leave a message at other times. An assigned nurse will contact patients on the second and fifteenth days to identify and resolve any CPAP-related issues. The SDC CPAP Questionnaire will be administered by the nurse for each patient in this group on day 2 following CPAP titration.

Patients in the usual care group will be advised to consult the CPAP technician for any questions or concerns.

Both groups of patients will be scheduled for follow-up appointments with a CPAP technician and a sleep physician on day 15 (only if the CPAP perception score is poor) and at 1, 3, and 6 months after starting CPAP therapy. During each visit, we will assess adherence to and tolerance of CPAP by asking questions about side effects and reviewing CPAP SD Card data. Any CPAP-related issues reported by the patients will be addressed accordingly. At the 6-month follow-up, all patients will be asked to complete the functional outcomes questionnaires once again (Figs 1 and 2). Sleep physicians involved in the routine clinical follow-up of the patients will be blinded to each patient’s treatment group.

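### The stated end date of 31 December 2025 falls before the month-6 visit of any patient recorded after about 16–23 June 2025, although screening stays open to July

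*Protocol article*

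**What the plan says.** The calendar and the fixed target are set in section 2.2 (Patients) of the protocol article. Patients will be "screened for eligibility between January 2025 and July 2025. Sixty patients will be included. The study will be terminated by December" 31, 2025.

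The follow-up clock is set elsewhere. Section 2.6 (Protocol study) says that "the patient will be scheduled to start CPAP therapy within 1–2 weeks after the nocturnal polygraph recording". Section 2.3.4 (Outcome measures) defines the primary outcome as "CPAP adherence measured in h/night at 1, 3, and 6 months after starting CPAP therapy", so time runs from CPAP start and not from screening or randomisation. The same section adds "Our secondary outcome is functional status at the 6-month follow-up", and section 2.6 applies this to everyone: "At the 6-month follow-up, all patients will be asked to complete the functional outcomes questionnaires once again". Section 3.2 (Limitations) confirms a follow-up of 6 months per patient.

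The article gives no visit window, no shorter follow-up for late entrants and no date for the last inclusion other than the July close of screening.

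**The concern.** Screening to July, a lag of 1–2 weeks and 6 months of follow-up add up to a last visit in early 2026, while the study is said to end in 2025. For a patient recorded in July these statements cannot all be true.

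The visit at risk matters. Month 6 is one of three time points of the primary outcome and the only post-treatment assessment of snoring, nasal obstruction, quality of life, fatigue, mood, cognition, insomnia and sleepiness. If the end date were enforced, late entrants would have no month-6 value, and the month-6 comparison would rest on fewer than the 30 patients per arm given in section 2.6.

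**Working it through.** **Inputs from the protocol article**
- Screening from January to July 2025; end of study 31 December 2025; 60 patients (section 2.2).
- 30 patients per arm; lag from polygraph to CPAP start 7–14 days (section 2.6).
- Month 6 counted from CPAP start (section 2.3.4).

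**Assumptions, not in the article**
- Screening opens on 1 January. The closing day in July is varied.
- Accrual is even over the window.
- Six months means calendar months.

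**Step 1. Can the stated end date be reproduced?**

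Month-6 date = polygraph date + lag + 6 months. For a polygraph on 31 July 2025:
- 7-day lag: CPAP start 7 August 2025, month 6 on 7 February 2026.
- 14-day lag: CPAP start 14 August 2025, month 6 on 14 February 2026.

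The end date of 31 December 2025 is not reproduced.

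**Step 2. The latest workable entry**

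31 December 2025 − 6 months gives 30 June 2025 as the last CPAP start. Subtracting 7 or 14 days gives 23 or 16 June 2025 as the last polygraph.

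**Step 3. How many patients could be affected**

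Share = days in the window after the last workable polygraph ÷ days in the window; count = 60 × share.

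| Screening closes | Days in window | Days too late (7 / 14-day lag) | Share | Of 60 patients |
|---|---|---|---|---|
| 1 July | 182 | 8 / 15 | 4.4% / 8.2% | 2.6 / 4.9 |
| 15 July | 196 | 22 / 29 | 11.2% / 14.8% | 6.7 / 8.9 |
| 31 July | 212 | 38 / 45 | 17.9% / 21.2% | 10.8 / 12.7 |

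With no lag at all and closure on 31 July, 31 of 212 days (14.6%, 8.8 patients) are still too late. With 6 months read as 180 or 182 days and a 7–14 day lag, the share for closure on 31 July is 16–20%. If all 60 polygraphs are done by 16 June, nobody is affected.

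**Step 4. What is not lost**

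For the latest entrant, month 3 falls on 7–14 November 2025, inside the study period. The 1- and 3-month adherence values are safe.

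**Step 5. Effect on precision, for illustration only**

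The article shows no power calculation and no SD. I took a difference of 1.5 h, the smallest of the three positive effects cited in section 1, and an assumed SD of 1.8–3.0 h, in a two-sided two-sample t-test at 5%.

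| Assumed SD (h) | Power, 30 per arm | Power, 25 per arm | Power, 24 per arm |
|---|---|---|---|
| 1.8 | 0.89 | 0.82 | 0.81 |
| 2.3 | 0.70 | 0.62 | 0.60 |
| 3.0 | 0.48 | 0.41 | 0.40 |

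Going from 30 to 25 per arm costs about 7–8 points. Losing 11–13 patients would leave 47–49, or 23.5–24.5 per arm; at 24 per arm the cost is about 8–10 points. The power levels depend heavily on the assumed SD. The size of the drop does not.

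**The case against.** The strongest reply is that the July date closes screening, while the sample is capped at 60. If the sixtieth patient is recorded by mid-June, the end date holds for everyone. That is right, and it is why no fixed count can be given. It does not remove the conflict: the article allows screening into July, and every inclusion from a July polygraph then breaks the end date at the stated lag.

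A reader might infer that about one patient in five will miss month 6. The article does not support that as a fact. The figure needs even accrual and screening to the last day of July, and neither is stated.

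A reader might also infer a biased comparison between arms, or month-6 data collected early to meet the deadline. The first does not follow: whether month 6 is reached depends on calendar entry date, which randomisation does not tie to arm. The second is conjecture, since nothing in the article suggests it.

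Nor can a particular power at month 6 be claimed, because the SD is an assumption.

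Finally, an article may leave detail to a fuller document. Here, however, the article prints the dates itself, and it is the printed dates that conflict.

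**Conclusion.** The concern holds as an inconsistency of dates. The July close of screening, the 1–2 week lag, the 6-month follow-up and the end on 31 December 2025 cannot all stand for a patient recorded after about 16–23 June 2025. This needs only the article's own figures and calendar arithmetic.

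Its size is conditional and runs from 0 to about 13 of 60 patients; the upper end assumes even accrual to 31 July and a 14-day lag. The consequence is missing month-6 data and lower precision at that time point. It should be corrected before the plan is followed as written, because month 6 is a primary time point and carries the whole secondary outcome, and because the correction is cheap.

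**What to change.** Reconcile section 2.2 with sections 2.3.4, 2.6 and 3.2 in one of two ways:

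1. Define the end of the study as the last randomised patient's 6-month visit plus its visit window. With screening to 31 July this is at least mid-February 2026; 28 February 2026 would leave two weeks after the latest visit date of 14 February.
2. Keep 31 December 2025 and state that the last CPAP start is 30 June 2025, so that the last polygraph for inclusion is about mid-June (16 June with a 14-day lag). This leaves no room for a visit window after the last due date and may make it harder to reach 60.

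In either case, state that the month-6 analysis is run only after the last randomised patient's month-6 visit, or its window, has passed.

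The first option costs a date update with the ethics committee and the registry and about two more months of follow-up (31 December to 28 February is 59 days). It needs no extra patients.

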### 2.3. Collected data

#### 2.3.1. Sociodemographic data.

The following sociodemographic data will be asked: age, sex, civil status, educational level, employment status, engagement in night work, nature of communities (urban or rural), socioeconomic level, social and health insurance scheme as well as anthropometric characteristics.

#### 2.3.2. Health status.

We will collect data on lifestyle habits related to alcohol and tobacco consumption, dietary habits, internet use, analgesics/anxiolytics/hypnotics consumption, physical activity, sleep-wake habits, and sleep duration. We will also collect data on prevalent morbidities such as nasal allergy, asthma, chronic obstructive pulmonary disease **(COPD)**, cardiovascular and metabolic diseases as well as depression.

#### 2.3.3. Nocturnal polygraph recording.

We will use an overnight type III PSG (Nox A1, ResMed, Australia) to diagnose OSAHS. The recording will be performed at home and include monitoring of respiratory flow using a nasal cannula, snoring with a contact microphone attached to the neck, thoracoabdominal movements using respiratory inductance respiratory **(RIP)** belts, transcutaneous arterial oxygen saturation **(SpO**_**2**_) and heart rate by pulse oximetry, as well as body position and sleep-wake pattern using actimetry. Each recording will be reviewed automatically followed by manual scoring according to the 2012 American Association of Sleep Medicine **(AASM)** manual for the scoring of sleep and associated events. The OAHI, the 3% oxygen desaturation index **(ODI)**, and the percentage of recording time with SpO_2_ levels below 90% **(T90%)** will be collected. OSAHS severity will be graded according to OAHI as follows: non-OSAHS < 5, mild OSAHS for 5 ≤ OAHI <15, moderate OSAHS for 15 ≤ OAHI < 30, and severe OSAHS for OAHI ≥ 30.

#### 2.3.4. Outcome measures.

Our prespecified primary outcome is CPAP adherence measured in h/night at 1, 3, and 6 months after starting CPAP therapy. Our secondary outcome is functional status at the 6-month follow-up, which includes snoring, nasal obstruction symptoms, subjective quality of life, fatigue, emotional status, cognitive function, insomnia and EDS.

**2.3.4.1. CPAP therapy**

AirSense S10 (ResMed) will be used for all enrolled patients with a pressure range of 4 cm H2O to 20 cm H2O. Each patient will be sized for an appropriate nasal CPAP mask from ResMed. After 2 weeks of at-home auto-CPAP titration, a fixed CPAP prescription follows according to data downloaded from the secure digital **(SD)** card of the device. The 95th percentile **(p95)** of the pressure titrated by Auto-CPAP will be used as a reference pressure level for fixed-CPAP therapy.

Data from the CPAP SD card, including residual AHI; total and daily usage time and air leak, will be recorded using the ResScan software. Good adherence to CPAP at 3 months will be defined as a CPAP use for ≥4 h per night on ≥ 70% of nights within a consecutive thirty-day period anytime during the last 90 days of therapy. To assess patients’ perception of CPAP therapy on the morning following the first night of CPAP titration, we will use the Sleep Disorders Center CPAP Questionnaire **(SDC CPAP questionnaire)**. This self-administered questionnaire includes 6 items scored on a 10-point Likert scale, with responses ranging from 1 (no difficulty/no discomfort/positive attitude toward CPAP) to 10 (significant difficulty/significant discomfort/ negative attitude towards CPAP). We used the mean CPAP perception score to create 2 categories of patients: poor CPAP perception (scores > 16) and good CPAP perception (scores ≤ 16). We hypothesized that a poor CPAP perception score would independently predict poor CPAP adherence during the first 30 days of therapy. [7].

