### 2.7. Statistical analysis

The data analysis will be conducted using SPSS Statistics for Windows, Version 23.0 (IBM SPSS Statistics for Windows, Version 23.0. Armonk, NY: IBM). We will use the Kolmogorov-Smirnov test to assess the normal distribution of data. Continuous variables with a normal distribution will be expressed as mean and standard deviation **(SD)**, while non-normally distributed variables will be represented as median and interquartile range **(IQR)**. For comparing means of 2 and 3 or more categories of normally distributed continuous variables, independent Samples t-test and ANOVA test will be used, respectively. Medians of non-normally distributed continuous variables will be compared using non-parametric tests (Mann-Whitney U test and Kruskal-Wallis). Categorical variables will be presented as counts and frequencies. The frequencies of categorical variables will be compared using Pearson χ2 or Fisher’s exact test, as appropriate. A significant level of p < 0.05 will be considered.

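### The CPAP-perception hypothesis claims independent prediction, but the listed tests are all unadjusted, and the score's scale, collection and link to the day-15 visit are inconsistently described

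*Protocol article*

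**What the plan says.** Section 2.3.4.1 (CPAP therapy) introduces the SDC CPAP questionnaire as a measure of how patients perceive CPAP on the morning after the first titration night: "This self-administered questionnaire includes 6 items scored on a 10-point Likert scale", each item running from 1 (favourable) to 10 (unfavourable). Patients are then divided in two: "We used the mean CPAP perception score to create 2 categories of patients: poor CPAP perception (scores > 16", with 16 or below counted as good. The hypothesis follows: "a poor CPAP perception score would independently predict poor CPAP adherence during the first 30 days of therapy".

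Section 2.7 (Statistical analysis) names the t-test and ANOVA for normally distributed variables and Mann-Whitney and Kruskal-Wallis otherwise. For categories, "The frequencies of categorical variables will be compared using Pearson χ2 or Fisher’s exact test, as appropriate". It names no regression or other adjusted method.

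Section 2.6 (Protocol study), in its paragraph on the education group, says: "The SDC CPAP Questionnaire will be administered by the nurse for each patient in this group on day 2". It then schedules both groups for follow-up "on day 15 (only if the CPAP perception score is poor", and again at 1, 3 and 6 months, and says that CPAP problems reported at visits will be dealt with. Section 2.5 (Usual care) states that control patients have no direct contact with investigators before the 1-month appointment.

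**The concern.** There are three separate difficulties.

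- **Claim and method do not match.** Independent prediction means that the association persists once other variables are held constant. No test in section 2.7 holds anything constant. A poor score could simply mark nasal obstruction, sleepiness or, if both arms are scored, treatment arm.
- **The predictor is not pinned down.** The article does not say on which scale 16 applies. It also gives differing accounts of who completes the form, how and when. The same cut-off decides who attends an extra visit, so the ambiguity reaches trial conduct as well as analysis.
- **The predictor changes care inside the outcome window.** A poor score leads to a day-15 visit at which problems are addressed. If that visit helps, poor scorers' 30-day usage moves towards that of good scorers and the association is diluted.

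At stake is a secondary claim: a published statement that early perception independently predicts adherence, resting on a crude comparison of perhaps 30 patients. The randomised comparison of education with usual care does not depend on it.

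**Working it through.** **1. Listed tests against the claim.** Section 2.7 names the t-test, ANOVA, Mann-Whitney, Kruskal-Wallis, Pearson chi-square and Fisher's exact test. Some handle three or more groups, but as described none includes a covariate. The most they can deliver here is a difference in adherence between poor and good scorers.

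**2. Scale of the cut-off** (six items, each 1 to 10, section 2.3.4.1).

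- Total: 6 × 1 = 6 to 6 × 10 = 60. A cut at 16 is attainable. It corresponds to 16 / 6 = 2.67 per item and lies (16 − 6) / (60 − 6) = 18.5% of the way up the range.
- Item mean: 1 to 10. A value above 16 cannot occur, so nobody would be classed as poor and the day-15 visit would never be triggered.
- Third reading: 16 is the average total in some sample, used as the dividing line.

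The article gives no inputs from which 16 could be reproduced, so the choice between readings cannot be settled from the text.

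**3. Who is scored.**

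| Item | Section 2.3.4.1 | Section 2.6 | Section 2.5 |
|---|---|---|---|
| Mode | completed by the patient | given by a nurse | – |
| Timing | morning after first titration night | day 2 | – |
| Patients | patients in general | only the education group is mentioned | – |
| Early contact | – | day-15 visit on a poor score, both groups | no direct investigator contact before month 1 |

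If the form is used only in the education group, the analysis has 30 patients and the day-15 rule cannot operate in usual care. If it is used in both groups, the analysis has 60, but section 2.6 does not describe how usual-care patients are scored, and section 2.5 has to be squared with a day-15 visit to a sleep physician.

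**4. Outcome window.** Days 1–14 precede the triggered visit: 14 / 30 = 47% of the window. The remaining 16 / 30 = 53% can be affected by it. As an illustration with assumed rates, take 30-day poor adherence of 50% in poor and 20% in good scorers, an equal split and two-sided alpha 0.05. Power = Φ[(Δ − 1.96·SE₀) / SE₁], with SE₀ pooled and SE₁ unpooled.

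- 60 patients: (0.300 − 1.96 × 0.1232) / 0.1169 = 0.50, power 69%.
- If the visit averts a quarter of poor adherence among poor scorers (50% to 37.5%): (0.175 − 1.96 × 0.1169) / 0.1147 = −0.47, power 32%.
- 30 patients: the same change takes power from 40% to 18%.

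**5. Cost of splitting the score.** This does not measure the missing adjustment; it shows why the continuous total is preferable. Adherence is measured in hours per night at month 1 (section 2.3.4), so the planned test for a two-category score is a t-test. The simulation used bivariate normal data, with the score either kept continuous or split at its mean. The correlation r is assumed; the article gives none.

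| r | Patients | Continuous score | t-test on split score |
|---|---|---|---|
| 0.3 | 30 | 37% | 25% |
| 0.4 | 30 | 60–61% | 41–42% |
| 0.5 | 30 | 83% | 63% |
| 0.4 | 60 | 90–91% | 73–74% |

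Where a range is shown, it is the spread between repeat simulations.

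**6. Why a linear model.** The article's only binary adherence definition is set for 3 months. At the 34.1% poor-adherence rate cited in the Background, 60 patients give 60 × 0.341 = 20 events and 30 patients give 10. That is about two parameters and one parameter at 10 events each. Hours per night avoids both problems.

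**The case against.** The strongest reply is that this is an unranked, exploratory aim in a condensed article. It is not among the primary or secondary outcomes and is absent from the abstract and the conclusion. A regression may sit in an analysis plan that is not shown. The sentences on the score are in the past tense and end with a citation, so they may partly restate the source study. This argument limits how serious the point is. It does not remove the mismatch: the article states a hypothesis and lists its methods, and those methods do not reach the hypothesis.

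Four stronger readings are tempting, and the documents do not support them.

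- *The hypothesis cannot be tested at all.* It cannot be tested with the listed methods. The data for an adjusted model are being collected, and usage on days 1–14 precedes the triggered visit.
- *The cut-off is impossible on its scale.* That is true only of an item mean. On the total, 16 is valid, and the fault is unclear wording.
- *Only the education group is scored.* Section 2.6 mentions only that group, but section 2.3.4.1 is general, the day-15 rule covers both groups, and the legend of Fig 2 (figure not shown) lists the questionnaire. Restriction to 30 patients is possible but not established.
- *The plan reduces to a 2×2 Fisher test with very low power.* Section 2.7 does not require hours per night to be split, so a Fisher comparison overstates the loss.

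**Conclusion.** The point holds, at modest weight. As written, the listed tests can support a crude association between perception and early adherence, but not independent prediction. That conclusion rests only on the text of sections 2.3.4.1 and 2.7.

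The scale of the cut-off is unstated, and sections 2.3.4.1, 2.5 and 2.6 disagree on the form's mode and timing, on who completes it, and on early contact in usual care. The triggered visit can affect about half (53%) of the outcome window. Dilution of the association follows only if the visit improves usage, which is an assumption.

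The power figures depend on an assumed correlation of 0.3–0.5, normal data and a split at the mean. They describe the loss from dichotomising and nothing else. The trial's main result is not affected.

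**What to change.** **Analysis.** Test the hypothesis by linear regression of month-1 hours per night on the continuous six-item total. Adjust for arm, if scores exist in both arms, and for a few prespecified baseline variables already collected (for example ESS, OAHI and NOSE). Alternatively, drop the word *independently* and report a crude association. Either way, label the result exploratory and describe it as prediction under the trial's own follow-up. Repeat it with usage on days 1–14 as a sensitivity analysis.

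**Text.** State whether 16 applies to the total or to another scale. Reconcile sections 2.3.4.1, 2.5 and 2.6 on who completes the form, how and when, and on the day-15 visit. Which arrangement is correct is for the sponsor to say.

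**Cost.** A few degrees of freedom, one added model and some clarifying sentences. The month-1 regression still includes days after the triggered visit, so the caveat remains. If usual-care patients turn out not to be scored, the sponsor should weigh that adding the form there would bring the score-triggered visit into the control arm. Keeping the analysis within the education group, without an arm term, avoids that at the price of 30 patients.
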